## Abstract

**Background:**

Placenta accreta (PA), a severe complication during delivery, is closely linked with massive hemorrhage which could endanger the lives of both mother and baby. Moreover, the incidence of PA has increased dramatically with the increasing rate of cesarean deliveries in the past few decades. Therefore, studies evaluating the effects of different perioperative managements based on different modalities in the treatment of PA are necessary. Among the numerous treatment measures, prophylactic abdominal aortic balloon occlusion (AABO) in combination with cesarean section for PA seems to be more advantageous than others. However, up to now, all studies on AABO were almost retrospective. Current evidence is insufficient to recommend for or against routinely using the AABO technology for control intraoperative hemorrhage in patients with PA. Thus, we hope to carry out a prospective, randomized controlled trial (RCT) study to confirm the effectiveness of the AABO technology in patients with PA.

**Methods/design:**

This trial is an investigator-initiated, prospective RCT that will test the superiority of AABO in combination with cesarean section compared to the traditional hysterectomy following cesarean section for parturients with PA. A total of 170 parturients with PA undergoing cesarean section will be randomized to receive either AABO in combination with cesarean section or the traditional hysterectomy following cesarean section. The primary outcome is estimated blood loss. The most important secondary outcome is the occurrence of cesarean hysterectomy during delivery; others include blood transfusion volume, operating time, neonate’s Apgar scores (collected at 1, 5 and 10 min), length of stay in intensive care unit, total hospital stay, and balloon occlusion-relative data.

**Discussion:**

This prospective trial will test the superiority of AABO in combination with cesarean section compared to the traditional hysterectomy following cesarean section for parturients with PA. It may provide strong evidence about the benefits and risks of AABO in combination with cesarean section for parturients with PA.

**Trial registration:**

Chinese Clinical Trial Registry, ChiCTR-INR-16008842. Registered on 14 July 2016.

**Electronic supplementary material:**

The online version of this article (doi:10.1186/s13063-017-1977-5) contains supplementary material, which is available to authorized users.

## Background

Placenta accreta (PA), a kind of morbidly adherent placenta, involves an absence of decidua basalis; the placenta always adheres to the underlying myometrium [1]. This morbidly obstetric condition is a severe complication during delivery. It is closely linked with massive hemorrhage, which could endanger the lives of both mother and baby [2, 3]. In patients with PA, median intraoperative blood loss is about 2000 ml during delivery, and in 10% of the cases it has been more than 10,000 ml in some institutions [4, 5]. Multiple pathophysiological conditions are involved in massive hemorrhage from patients with PA during cesarean section, including pelvic viscera injury to the bladder, ureter, bowel, or other organs during the surgery. When massive hemorrhage cannot be effectively controlled, multisystem organ failure (MOF) and disseminated intravascular coagulation (DIC) will follow [6]. Therefore, placenta accreta poses a serious threat to the safety of the mother.

However, in recent years, the incidence of PA has risen with the increasing rate of cesarean deliveries [7]. According to a World Health Organization (WHO) report, China has become the country with the highest rate of cesarean sections, up to 68%. China will face a big challenge with its two-child family policy initiation. In America, the cesarean delivery rate will be 56.2% if the cesarean rate continues to grow as it has in the past, and there will be 6236 patients with placenta previa, 4504 patients with placenta accreta, and 130 maternal deaths annually [8]. Therefore, studies evaluating the effects of different perioperative management approaches based on different modalities in the treatment of placenta accreta are necessary.

In the traditional method, hysterectomy following cesarean section is usually indicated as the treatment option in patients with morbidly adherent placenta. This treatment reduces maternal morbidity, but it results in infertility [9]. To minimize intraoperative hemorrhage and facilitate surgery, some novel treatment options have been described, including proximal ligation of the internal iliac artery or uterine artery and vascular balloon catheters placed in the iliac artery, uterine artery, or even the abdominal aorta [10]. Among the numerous treatment measures, prophylactic balloon occlusion of the abdominal aorta seems to be more advantageous than others [11, 12]. Recently, a large-sample retrospective study from our single center also shows that prophylactic abdominal aortic balloon occlusion (AABO) has a promising future [13, 14]. These retrospective studies strongly suggest that we need an adequately powered prospective study to demonstrate the benefits and risks. Thus, the primary aim of the study is to investigate the benefits and risks of AABO in combination with cesarean section for PA.

## Methods/design

### Trial design

This protocol was developed in accordance with the Standard Protocol Items: Recommendations for Interventional Trials (SPIRIT) Statement. For the SPIRIT checklist see Additional file 1, and for the SPIRIT figure see Additional file 2. This trial is an investigator-initiated, prospective, randomized controlled trial (RCT) that will test the superiority of AABO in combination with cesarean section compared to the traditional hysterectomy following cesarean section for parturients with PA. A brief flow diagram of the study is shown in Fig. 1.

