### Trial interventions

All patients will receive the standard multidisciplinary team service (including the senior obstetrician, gynecologist, anesthesiologist, neonatology teams, urologist, imaging doctor, and adequate number of blood units in the operating room). The antepartum diagnosis of PA is made clinically, based on the pelvic ultrasound or MRI. Pregnant woman with PA diagnosed by ultrasound or MRI will be recruited in this study. In both groups, pregnant woman will undergo the standard protocol, as described previously [14]. Considering the risk of massive bleeding complicated by profound hypotension and coagulopathy, we choose general anesthesia for all patients with PA [17, 18]. Endotracheal intubation is performed with the use of a rapid sequence induction (RSI) technique [19, 20]. We monitor invasive arterial blood pressure (ABP), electrocardiogram (ECG), SPO_2_, PetCO_2_, temperature (T), arterial blood gas (ABG), and thrombelastograph (TEG) of the patients during the operation. After fetal delivery and umbilical cord clamping, according to the PA location and depth, patients are given local excision of the uterine wall, placenta evacuation, partial cystectomy, and bladder repair. 20 U of oxytocin and 250 μg of tromethamine are injected in the myometrium.

In the traditional group, patients are given a cesarean section without AABO. In this group, conservative treatments for PA, including oversewing of the placental bed, a uterine tamponade, and bilateral uterine artery, ligation are used. Hysterectomy is performed when massive hemorrhage cannot be controlled.

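### The objective names hysterectomy as the control treatment, but the interventions section gives controls uterus-sparing surgery with hysterectomy only as rescue

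*Protocol article*

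**What the plan says.** **Objective and randomized treatment.** Trial design tests the superiority of AABO plus cesarean section "compared to the traditional hysterectomy following cesarean section for parturients with PA". The abstract's Methods/design paragraph goes further and says that parturients are "randomized to receive either AABO in combination with cesarean section or the traditional hysterectomy following cesarean section". The abstract's Discussion paragraph repeats the aim: to "test the superiority of AABO in combination with cesarean section compared to the traditional hysterectomy following cesarean section for parturients with PA". Background gives the wording a plain meaning. In the traditional method, "hysterectomy following cesarean section is usually indicated as the treatment option in patients with morbidly adherent placenta", and infertility is named as its consequence.

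**Control arm as described for delivery.** Trial interventions says: "In the traditional group, patients are given a cesarean section without AABO". It continues: "In this group, conservative treatments for PA, including oversewing of the placental bed, a uterine tamponade, and bilateral uterine artery, ligation are used". It ends: "Hysterectomy is performed when massive hemorrhage cannot be controlled".

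**Outcome that depends on the answer.** The abstract states: "The most important secondary outcome is the occurrence of cesarean hysterectomy during delivery". Secondary outcomes lists it, and Statistics assigns it a chi-square test.

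**The concern.** A superiority trial needs one named comparator. Here the hypothesis names one treatment and the operational section describes another. Nothing is merely left out for brevity: both descriptions are affirmative statements in the current text, so a fuller protocol could not make both true.

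Two things are at stake. The first is the conclusion. If controls receive the conservative strategy, a positive result written in the words of the objective would claim superiority over a treatment to which no control patient was assigned. The second is the leading secondary outcome. Cesarean hysterectomy says something about AABO only if it is not itself the assigned control treatment.

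**Working it through.** **1. The two versions side by side**

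| | Version A: Abstract, Trial design | Version B: Trial interventions |
|---|---|---|
| Assigned control treatment | Hysterectomy following cesarean section | Cesarean section, no balloon, conservative measures |
| Role of hysterectomy | The treatment itself | Rescue for uncontrolled bleeding |
| Hysterectomy rate in controls | About 100% by assignment | To be observed |
| What a positive trial would show | AABO better than planned hysterectomy | Adding AABO better than not adding it |

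**2. Does other text settle it?** Not fully.
- For A: the account of the traditional method in Background.
- For B: the main Discussion lists emergent hysterectomy as the last of several traditional measures. The aim at the end of Background names no hysterectomy comparator. Trial interventions describes uterine wall excision and placenta evacuation before it separates the arms. Hysterectomy is also listed as an outcome.
- The word traditional does not help. Background counts uterine artery ligation among the novel options, Trial interventions puts it in the traditional group, and the main Discussion calls it traditional.

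**3. Sample size.** Inputs from Sample size: expected difference 1000 ml, SD 355 ml, clinically important difference 800 ml, 2.5% level (taken as one-sided), power 0.90. With 800 ml acting as a superiority margin, the effective difference is 1000 − 800 = 200 ml:

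n = 2 × (1.960 + 1.282)² × 355² / 200² ≈ 66.2, so 67 per group, as stated.

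Dropout: 67 / 0.80 = 83.75, so 84 against the stated 85. The choice of comparator does not enter this arithmetic. The 2000 ml control figure is given for PA at delivery with no management named, so it does not decide between A and B.

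**4. What the hysterectomy test would mean.** The documents give no hysterectomy rates, so every rate below is an assumption. Two-sided 0.05, n per group:

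power = Φ{ [ |p₁ − p₂| − 1.96 √(2p̄(1 − p̄)/n) ] / √( [p₁(1 − p₁) + p₂(1 − p₂)]/n ) }

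Example, 30% against 10% with n = 67: (0.200 − 1.96 × 0.0691) / 0.0669 ≈ 0.96, so power is 0.83.

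| Control vs AABO | Version | n = 67 | n = 85 |
|---|---|---|---|
| 99.9% vs 80% | A | 0.976 | 0.994 |
| 99.9% vs 50% or 30% | A | about 1.0 | about 1.0 |
| 50% vs 30% | B | 0.66 | 0.76 |
| 30% vs 10% | B | 0.83 | 0.91 |
| 20% vs 5% | B | 0.75 | 0.85 |
| 10% vs 2% | B | 0.50 | 0.60 |
| 5% vs 1% | B | 0.27 | 0.33 |

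A check by hand under A, with an assumed 76 of 85 hysterectomies in the AABO arm and 85 of 85 in controls: χ² = 170 × (9 × 85)² / (85 × 85 × 161 × 9) = 9.50, p = 0.002. An AABO arm in which 89% had a hysterectomy would still be significantly better, because the control figure was fixed by assignment. Under B the result depends on the rates that occur.

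**The case against.** The strongest reply is that the control arm is defined. Trial interventions is the only operational description, it is specific, and the main Discussion and the choice of hysterectomy as an outcome both fit it. On this view the objective uses a loose label. Much of this stands: the text leans toward the conservative strategy, and a reader who infers that the comparator or the hysterectomy outcome is undefined goes too far. Cesarean hysterectomy is a named event with a named test. What does not stand is that the label is harmless, because the abstract makes hysterectomy the treatment patients are randomized to receive, and Background explains it as hysterectomy proper.

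Three other inferences are tempting and unsupported.
- That the hysterectomy comparison is decided in advance. This holds only if the objective is taken literally, and Trial interventions contradicts that. The 80% and 76/85 figures are illustrations, not forecasts.
- That the sample size fails. The 67 per group is unchanged, and what lies behind the 2000 ml figure rests on a cited source not shown.
- That the two arms use different hysterectomy thresholds. The rule is written only under the traditional group, but the same section refers both groups to a standard protocol published elsewhere, so absence from this article proves nothing.

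The main Discussion does not repeat the hypothesis. The hysterectomy wording there is confined to the Discussion paragraph of the abstract.

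**Conclusion.** The concern holds as an internal contradiction. The comparator in the abstract and Trial design is not the one in Trial interventions, and the meaning of the most important secondary outcome depends on which applies. It is informative under the interventions text and about 100% in controls by assignment under the objective. Left as written, the trial either claims superiority over a treatment its controls were not assigned, or tests an outcome that its own allocation fixes. The definition of the primary outcome, its test and the sample size arithmetic are unaffected, although the conclusion drawn from blood loss must name the comparator actually used. The finding rests on the current wording alone. The power figures add only illustration and depend on assumed rates. Which control treatment is clinically right is not judged here.

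**What to change.** Reconcile the abstract (Methods/design and Discussion paragraphs) and Trial design with Trial interventions before the first patient, and use one control-arm description throughout. Trial status says recruitment had not begun at publication, so there should be time.

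- If the Trial interventions version is the one delivered, state the hypothesis and conclusion as AABO plus cesarean section versus cesarean section without AABO. Make no claim of superiority over planned hysterectomy. Hysterectomy can then stay as a tested outcome.
- If hysterectomy is the assigned control treatment, correct Trial interventions and do not test the occurrence of hysterectomy as an outcome.

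The hysterectomy rule is stated only under the traditional group. The clinical team should reconcile how it relates to the AABO arm. No criterion is proposed here.

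The cost under the first option is wording alone. The second also drops one secondary test. Neither changes the arithmetic behind 67 per group.

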**Fig. 1 Fig1:**
[figure not shown]
Flow diagram of the study

### Recruitment

From June 2016 to December 2018, a total of 170 patients diagnosed with PA, based on the obstetrician’s knowledge and experience and on an ultrasound or magnetic resonance imaging (MRI) examination [15, 16], will be enrolled in this study at the First Affiliated Hospital of Zhengzhou University.

### Enrollment criteria

All the subjects must meet the following inclusion criteria:Patient diagnosed with PA based on obstetrician’s knowledge and experience and on ultrasonic or MRI examinationUndergoing elective or emergency cesarean section

The exclusion criteria are as follows:Patient’s or relative’s refusal to participateUncontrolled sepsis or infection of femoral artery puncture site in inguinal regionSevere peripheral vascular diseaseAortic diseases including, e.g., aortoarteritis, aortic aneurysm, dissection of aorta, and aortic regurgitation, etc.Severe cardiac disease

### Randomization, allocation concealment, and blinding

Subjects who meet the eligibility criteria will be randomly assigned to either the traditional treatment group or the interventional treatment group. Group assignments are generated using a computer algorithm (Winpepi version 11) that allocates patients in equal numbers to both groups. The randomization list will be sealed in sequentially numbered opaque envelopes, which will be stored in a double-locked cabinet. Randomization is implemented by a research assistant who is not involved in recruitment. After random assignment, the envelopes will again be stored separately in a double-locked cabinet. Allocation concealment will not be broken until the trial is complete.

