### Sample size

The sample size was calculated to compare two proportions with two-sample noninferiority or superiority. According to Muñoz et al., median blood loss was 2000 ml in parturients with PA during delivery [23]. The study of Panici et al. showed that median blood loss was 950 ml in parturients with AABO at cesarean section [24]. Considering a difference in volume of bleeding of 1000 ml with a standard deviation of 355 ml [13] in two treatment groups, a difference of 800 ml between two treatment groups is considered to be clinically important. Assuming the difference between two groups at a 2.5% significance level and a power of 0.90, 67 patients in each group are required for a comparison within the groups. Considering an estimated 20% dropout rate, 85 patients in each group for a total of 170 patients will be included in this study.

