### Statistics

An intention-to-treat analysis will be performed to compare all primary and secondary outcomes in the future study. Continuous variables will be described as means ± standard deviation (SD). Categorical variables will be described as percentages. Demographic data, blood transfusion volume, operating time, length of stay in the ICU, total hospital stay, and EBL will be analyzed by Student’s *t* test to compare the two methods. The occurrence of CH during delivery will be compared by the chi-square test. The neonate Apgar scores will be analyzed using the Mann-Whitney *U* test.

The statistical analyses will be carried out with SPSS software (SPSS, Inc., Chicago, IL, USA). The statistical significance will be considered with a two-tailed *P* value <0.05 and a one-tailed *P* value <0.025.

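### A single list balanced only on numbers, followed by unadjusted tests, gives up some precision and baseline balance on placental depth and urgency; the comparison itself stays valid

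*Protocol article*

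**What the plan says.** All references are to the protocol article.

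- *Randomization, allocation concealment, and blinding*: "Group assignments are generated using a computer algorithm (Winpepi version 11) that allocates patients in equal numbers to both groups". The result is one list in one run of envelopes: "The randomization list will be sealed in sequentially numbered opaque envelopes". No stratum, block or minimisation factor is named.
- *Enrollment criteria*: any placenta accreta diagnosed by the obstetrician with ultrasound or MRI is eligible, without a limit on depth, and so is "elective or emergency cesarean section".
- *Trial interventions*: after delivery and cord clamping, "according to the PA location and depth, patients are given local excision of the uterine wall, placenta evacuation, partial cystectomy, and bladder repair". The article therefore expects depth to vary among enrolled patients and to shape the operation.
- *Statistics*: "length of stay in the ICU, total hospital stay, and EBL will be analyzed by" Student's t test. Hysterectomy is compared by a chi-square test. No covariate is named for either.

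**The concern.** Depth is treated as a determinant of the surgery, so it is a natural prognostic factor for blood loss and hysterectomy. Urgency is a plausible second one. Neither is used to balance the arms, and neither enters the tests that the article names. A chance difference in either factor would therefore stay in the reported comparison uncorrected, and any variance that they explain would stay in the error term.

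At stake are the width of the confidence interval and how convincing the baseline table looks. Stratification also has to be settled before the first envelope is opened. Adjustment can be added later, but only for factors that were recorded before allocation.

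**Working it through.** **1. The plan's own sample size.** Inputs from *Sample size*: an expected gap of 1000 ml, an SD of 355 ml, 800 ml as the size of effect that the plan regards as mattering to patients, a 2.5% level, power 0.90, and 67 per arm as the answer. The stated figure is reproduced if 800 ml acts as a superiority margin, so that the effective difference is 1000 − 800 = 200 ml, with one-sided 2.5%:

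n per arm = 2 × [(1.960 + 1.282) × 355 / 200]² = 66.2, so 67.

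With 20% dropout, 67 / 0.8 = 83.75, so 84; the plan states 85. Stratifying alters none of these inputs.

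**2. Chance imbalance under an 85:85 split.** The article gives no case mix, so the share p of patients with the factor (deep invasion, say) is assumed. With K = 170p such patients, the number falling in one arm is hypergeometric, with variance 85 × p(1 − p) × 85/169. The SD of the between-arm difference in share is 2/85 times the square root of that variance. For p = 0.3: variance 8.98, root 3.00, SD 7.1 points.

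| Assumed share | K of 170 | SD of difference | P(10 points or more) | P(15 or more) | P(20 or more) |
|---|---|---|---|---|---|
| 20% | 34 | 6.2 points | 8.3% | 1.2% | 0.1% |
| 30% | 51 | 7.1 points | 18.0% | 4.4% | 0.7% |
| 50% | 85 | 7.7 points | 22.0% | 6.5% | 1.4% |

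At 67 per arm, the probabilities of 10 points or more are 19.6%, 18.6% and 30.0%.

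**3. What stratified blocks would leave.** Take two factors with two levels each, hence four strata. With blocks of 4, an unfinished block leaves the arms at most 2 patients apart in a stratum. Each factor level spans two strata, so the gap is at most 4 patients, or 4/85 = 4.7 points. If blocks run up to 6, the limits are 3 per stratum and 6 per level, or 6/85 = 7.1 points.

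**4. What adjustment would gain.** Adjusting for factors that explain a share R² of the variance multiplies the standard error by √(1 − R²). For a binary factor with effect d and within-stratum SD w, R² = p(1 − p)d² / [p(1 − p)d² + w²]. Assume p = 0.3 and d = 1000 ml:

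- w = 2000 ml: 210,000 / 4,210,000 = 0.050; √0.950 = 0.975, a standard error 2.5% shorter.
- w = 1000 ml: 210,000 / 1,210,000 = 0.174; √0.826 = 0.909, about 9% shorter.

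On the plan's terms (67 per arm, 200 ml, SD 355 ml), power is 90.3% unadjusted and would be 93.0% at R² = 0.1.

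**5. Whether the imbalance can be set in millilitres against the planned standard error.** That standard error is 355 × √(2/85) = 54 ml. With p = 0.3 and d = 1000 ml, the imbalance has an SD of 0.0705 × 1000 = 71 ml. But these inputs imply a severity SD of √0.21 × 1000 = 458 ml, already above the planned total SD of 355 ml. A total SD of 355 ml caps d at 355/√(p(1 − p)): 888, 775 or 710 ml for p = 0.2, 0.3 or 0.5. With w = 1000 ml, the matching total SD is √1,210,000 = 1100 ml and the matching standard error 1100 × √(2/85) = 169 ml. The 71 ml is a component of that 169 ml (70.5²/168.7² = 0.17, the same R² as in step 4).

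**The case against.** **Unstratified equal allocation is a legitimate design.** This stands. The article contradicts nothing here, and stratifying is an improvement rather than the correction of an error.

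**Silence in a condensed article is not proof.** Strata and covariates may be set out in the full protocol or analysis plan, which are not shown. This stands in part: the absence of stratification is inferred. However, the article is specific about software, version, ratio, envelopes and tests, and what it describes is one list and unadjusted tests. If the full protocol already stratifies and adjusts, the point falls away.

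**Some premises are clinical judgement.** The article ties depth to the operation, but nowhere says that urgency affects blood loss or hysterectomy. Nor does it say that the qualifying scan is graded for depth; it mentions depth when describing surgery after delivery. Both limits stand.

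**Stronger readings that a reader might infer, and that the document does not support:**

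- *That chance imbalance could exceed the planned standard error.* Step 5 shows that this sets a severity effect that is impossible under an SD of 355 ml against a standard error built on that SD. Within one consistent set of figures, imbalance is part of the standard error and cannot exceed it.
- *That the result could not be told apart from case mix.* Randomisation keeps the type I error, and the standard error already allows for such imbalance.
- *That the extreme losses cited in the Background (above 10,000 ml in 10% of cases in some institutions) define a severe baseline subgroup.* They describe an outcome, are not linked to depth or urgency, and cannot be stratified on.

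**Conclusion.** The point holds as a matter of efficiency and baseline balance, not of validity. The protocol article balances numbers only and names unadjusted tests, in a population whose surgery it says varies with depth. An imbalance of 10 points or more in a relevant factor is far from rare (about 8% to 22%), while one of 20 points or more is unlikely (at most 1.4%). The gain in standard error from adjusting is modest, about 2.5% to 9%.

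These sizes rest on an assumed prevalence of 20% to 50% and an assumed R² of 5% to 17%; the document supplies neither. The R² values were derived with within-stratum SDs of 1000 and 2000 ml, so they should be read as shares of variance and not combined with the planned 355 ml into a shift in millilitres. Severity is minor to moderate.

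**What to change.** **Randomisation section.** Before the first allocation, generate the list in permuted blocks of varying size within four strata: elective v emergency section, and two classes of depth assessed on the qualifying ultrasound or MRI. Define the depth classes, and record the class before the envelope is opened. Keep one numbered envelope series per stratum.

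**Statistics section.** Analyse blood loss with a linear model containing arm and the two factors, and report the adjusted difference with its confidence interval. Compare hysterectomy with a stratified method such as Mantel-Haenszel.

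**If stratified lists are no longer possible**, adjust for the same factors as recorded before allocation. Check this first: *Trial status* says recruitment has not begun, while *Recruitment* gives enrolment from June 2016.

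**Cost.** The sample size does not change. The work is a new list, four envelope series, one extra baseline item and two model terms. The real burden is classifying depth before allocation, sometimes in an emergency. Some patients will be misclassified, which reduces the gain without biasing the comparison. Strata may be small: if each factor were present in 20% of patients, independently, the smallest would expect 170 × 0.2 × 0.2 = 6.8 patients, so blocks should be short.
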